### 2.11. Participant Timeline

Participants' timeline is given in Table 3.

### 2.12. Statistical Methods

All analyses will be based on the intention-to-treat (ITT) principle. Missing data will be reduced to a minimum. For data loss caused by subject drop-out, data from the previous measurement will be carried forward. The frequency, percentages, means and standard deviations, medians, and quartiles will be calculated for descriptive analysis. Intergroup comparisons of continuous variables will be performed using the *t*-test or Mann–Whitney *U* test. Categorical variables will be compared using Pearson *χ*^2^ tests or Fisher exact tests. Time-to-event outcomes will be analyzed using the Kaplan–Meier method and Cox proportional hazard models. Two-tailed *p* < 0.05 will be considered statistically significant for all analyses. All statistical analyses will be conducted using SPSS version 25.0 for Windows (IBM Corporation, Armonk, NY, USA).

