## 2. Methods

### 2.1. Objectives

The recurrent attacks of AR are one of the main issues that affect patients. However, most of the pharmacological management approaches recommended in the guidelines of AR have not been evaluated for their efficacy in controlling recurrences. Our previous clinical observations showed that MYN achieved several advantages in treating allergic rhinitis, especially in controlling recurrences. Therefore, this study was designed to provide more substantial evidence for the efficacy and safety of MYN in preventing the recurrence of AR.

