### 2.8. Randomization and Blinding

This study adopted a multicenter, open-label, randomized, and parallel-arm controlled design. The randomization method was stratified block randomization. The patients were stratified based on the three different centers, and the ratio of the experimental group to the control group was 1 : 1. According to the given number of seeds and the appropriate length of the segment selected, an independent clinical statistician will use SAS 9.4 statistical software to generate a random sequence and save it as a file in a sealed envelope and then distribute the corresponding envelopes to each center. An independent statistician will keep all of the methods, processes, results, and envelopes of the random sequence. After the beginning of the study, the envelopes will be opened in order of grouping, and recruited subjects will be assigned to treatment groups according to the information in the envelope. Any randomized subject will retain their randomization number after withdrawing from the study for any reason. The random number corresponding to this subject will not be allowed to be reused by other new subjects. Only outcome assessors, examiners, and data analysts will be blinded in this study. Subjects and researchers will not be blinded due to the differences in the color and odor between MYN and the mometasone furoate aqueous nasal spray.

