#### 2.10.5. Safety Assessment

Vital signs, ECG, and laboratory tests (liver and kidney function and blood and urine routine examination) will be compared before and after interventions, and the safety of the interventions will be assessed when AR is controlled. The subjects should contact the researchers if any side effects or adverse events occur. After receiving the patient's feedback, investigators will inform the subjects to visit the hospital for further assessment. In addition, a urine pregnancy test should be performed before female subjects of childbearing age are recruited.

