### 2.15. Criteria for Adverse Event Reporting and Discontinuing or Modifying the Allocated Interventions

Subjects may refuse to participate in the study or withdraw from the study at any time during the study without affecting their medical treatment and benefits. If a patient is uncooperative, the investigators can also end the patient's participation in this study. The investigators will make a follow-up appointment (by phone, e-mail, and message), contact the subject if possible, inquire about the reason for withdrawing, the time of last medication, and complete as many assessment items as possible. If any adverse event (AE) occurs during the trial, the responsible investigator should take the necessary measures to provide treatment. Any serious adverse events (SAEs) will be reported within 24 h to the sponsor and the ethics committee. The manifestation, severity, onset time, duration, and prognosis of the adverse events will be observed and recorded in detail. A committee of medical experts will determine whether it is related to the treatment. In the case of AE and injuries caused by diagnostic tests or research drugs, effective measures should be taken to ensure the safety of the subjects. Moreover, the research team will pay the related treatment costs and the corresponding economic compensation according to China Good Clinical Practice Guideline.

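### Intention-to-treat is fixed for all analyses with no exemption for safety, so patients who never used a spray would count in the harm denominator of their allocated arm

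*Protocol article*

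**What the plan says.** Section 2.12 (Statistical Methods) sets one principle for everything: "All analyses will be based on the intention-to-treat (ITT) principle". It does not separate efficacy from safety.

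Safety is a declared aim. Section 2.1 says the study is meant to "provide more substantial evidence for the efficacy and safety of MYN in preventing the recurrence of AR". Section 2.10.5 (Safety Assessment) lists vital signs, ECG and laboratory tests, which "will be compared before and after interventions, and the safety of the interventions will be assessed when AR is controlled". Adverse events come in by self-report: "The subjects should contact the researchers if any side effects or adverse events occur". Neither that section nor section 2.15, on adverse event reporting, names an analysis set or a denominator.

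Two further statements bear on who stays in the count. Section 2.15 says "Subjects may refuse to participate in the study or withdraw from the study at any time during the study". Section 2.8 says "Any randomized subject will retain their randomization number after withdrawing from the study for any reason". Section 2.8 also makes clear that patients and researchers know the allocation.

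**The concern.** For the superiority comparison of recurrence, analysing by allocation is the usual cautious choice, because non-adherence tends to pull the arms together. For harms the same dilution is not cautious. A patient with no exposure cannot have an event caused by the spray, yet adds one to the denominator. The arm's harm rate then falls below the rate among people who actually used the product, which is the figure a prescriber wants.

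At stake is the safety statement for a new nasal product set against mometasone. Under the sentence in section 2.12, the as-randomised harm table is the only one specified. A later analysis plan that defined an exposed safety set would contradict the published sentence.

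**Working it through.** **Inputs from the article.** Section 2.6 gives 86 per group and 190 in total; section 2.2 gives 1:1 allocation. The sample size reproduces with unpooled variance and the 5% margin:

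n = [0.75 × 0.25 + 0.50 × 0.50] × (1.960 + 0.842)² / (0.25 − 0.05)² = 85.85, so 86 per arm.

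86 × 1.1 = 94.6, so 95 per arm and 190 in total. This point disputes neither figure and changes neither. The 95 serves only as the arm size below.

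**Inputs that are assumed.** The article gives no adverse event rate and no non-use rate. All rates below are illustrative.

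**Step 1: rate in one arm.** With k never-users among 95 and no events in never-users:

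reported rate = rate among users × (95 − k) / 95

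| Rate among users | k = 5 | k = 10 |
|---|---|---|
| 20% | 18.9% | 17.9% |
| 30% | 28.4% | 26.8% |

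Never-users may still report unrelated events. With an assumed 2% background rate and k = 10, the 20% becomes (85 × 0.20 + 10 × 0.02) / 95 = 18.1% instead of 17.9%. The direction is unchanged as long as the background rate is below the rate among users.

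**Step 2: difference between arms, equal non-use.** Let a share u in each arm be never-users with background rate b. Each arm's rate is (1 − u) × own rate + u × b. The background term cancels, so the difference is (1 − u) times the true difference. With 20% against 10%:

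- u = 2%: 9.8 points
- u = 5%: 9.5 points
- u = 10%: 9.0 points

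At 95 per arm and two-sided 0.05, power for this contrast is 48.8% with full exposure, 46.3% at u = 5% and 43.7% at u = 10%.

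**Step 3: difference between arms, unequal non-use.** Take 10% against 15% among users (true difference 5.0 points), a 2% background, and 10% never-users in one arm only.

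- Non-use in the lower-harm arm: 0.9 × 10% + 0.1 × 2% = 9.2%; difference 15.0 − 9.2 = 5.8 points, so it widens.
- Non-use in the higher-harm arm: 0.9 × 15% + 0.1 × 2% = 13.7%; difference 13.7 − 10.0 = 3.7 points, so it shrinks.

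**Step 4: scale.** At a 20% rate in both arms of 95, the 95% half-width for a difference is 1.96 × √(2 × 0.2 × 0.8 / 95) = 11.4 points. The shifts above are well inside sampling error.

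**The case against.** The strongest reply is that a safety set is routine content for an analysis plan or full protocol. Section 2.12 compresses all statistics into one paragraph, and section 2.17 says the complete protocol is on the registry. Silence on a safety set would indeed be no fault. But the article is not silent: it makes a universal statement that covers safety, so the matter is a rule that is stated too widely.

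A second reply is that a committee of medical experts judges relatedness event by event (section 2.15), which guards against blaming a drug the patient did not use. That stands for attribution of single events. It does not alter the denominator, and it does not touch the vital signs, ECG and laboratory comparisons.

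A third reply is that harms by allocated arm are a valid randomised comparison and that grouping by spray used gives this up. That is correct, and it is why the as-randomised table should be kept as a supplement.

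Several stronger readings are tempting but not supported:

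- A reader might take the 10% in section 2.6 as the expected share of never-users. It is an allowance for loss to follow-up, and a patient lost after starting treatment was exposed and belongs in the safety set.
- A reader might infer that events will be booked to the wrong drug. No passage points to patients using the other spray.
- A reader might infer that open allocation will lead patients to refuse on learning their arm. The right to withdraw in section 2.15 is general and says nothing about refusal at that moment.
- A reader might conclude that the comparison is always biased towards no difference. Step 3 shows that unequal non-use can move it either way.

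**Conclusion.** The point holds as a fault of wording with a modest consequence. Followed literally, section 2.12 puts never-dosed patients into the harm denominator of their allocated arm and lowers that arm's reported harm rate, provided non-users have fewer events than users. The between-arm difference shrinks under similar non-use and is unpredictable under unequal non-use.

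The size is unknown and probably small. Under the assumed 20% rate and 5 to 10 never-users of 95, the reported rate drops by about 1 to 2 points; at 30% it drops by about 2 to 3 points. A safety conclusion is unlikely to turn on this alone. It merits correction because the correction is nearly free.

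**What to change.** Limit the sentence in section 2.12 to efficacy, and add a rule for safety along these lines: *Efficacy analyses follow the intention-to-treat principle. The main safety analysis (adverse events, vital signs, ECG, laboratory tests) includes all patients who used at least one dose, grouped by the spray actually used. A harm table by allocated arm is given as a supplement.* Report, for each arm, how many patients were never dosed and how many used the other spray.

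The cost is one extra analysis-set flag and a record of first use. Section 2.13 mentions a medication compliance index but does not define it, so it cannot be assumed to capture first use; a single field in the case report form would do. The main safety comparison is then no longer strictly as randomised, which the supplementary table covers. No extra patients or visits are needed, and the sample size is unchanged.

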**Methods:**

In this study, a multicenter, open-label, randomized, and parallel-arm trial will be conducted at three study centers. A total of 190 subjects aged 18–65 with persistent and moderate-severe AR (Qi deficiency and blood stasis syndrome) will be randomly assigned to receive the modified Yupingfeng nasal spray or mometasone furoate aqueous nasal spray. When subjects' rhinitis control assessment test (RCAT) score is >21 for two weeks, they will stop taking the medication and enter the follow-up. Once a relapse occurs, the time point will be recorded, and the follow-up stops. The primary outcome is the six-month recurrence rate of AR after intervention withdrawal. The secondary outcomes are the one-month recurrence rate of AR, the RCAT score, the duration of follow-up, the duration of medication, the nasal endoscopic results, and questionnaires to evaluate symptoms, signs, and quality of life. The mechanism outcomes include some indicators that may be associated with AR recurrence. In addition, electrocardiograms and other safety indicators will be applied to evaluate the drug's safety. *Discussion*. This is the first study to explore the efficacy of traditional Chinese medicine nasal spray on AR from the perspective of controlling recurrence. The results of this trial may provide valuable clinical evidence for controlling the recurrence of this disease by pharmacotherapy. *Trial Registration*. This study was registered with registration number ChiCTR2100047053 (Chinese Clinical Trial Registry, https://www.chictr.org.cn/showproj.aspx?proj=127432 on June 7, 2021).

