### 2.6. Sample Size

In this study, the 6-month recurrence rate was used as the basis for sample size estimation. Combined with our previous research and the literature, the six-month recurrence rates of AR treated with MYN and mometasone furoate aqueous nasal spray were approximately 50% and 75% [27], respectively. Using 5% as the superiority margin, an acceptable alpha of 2.5% (one-tailed), and an acceptable beta of 20%, 86 participants were required in each group. To allow for a 10% loss to follow-up, we will recruit 190 subjects in total.

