#### 2.10.2. Primary Outcomes

The primary outcome is the six-month recurrence rate of AR after intervention withdrawalFollow-up: subjects will enter the follow-up period after withdrawal of medications. Once a relapse occurs, the patient's recurrence time will be recorded, and the follow-up ends. Otherwise, the follow-up will continue until six months after drug withdrawal.Definition of recurrence/relapse: when the RCAT score ≤21 during follow-up, the patient will be considered in a relapse stateDefinition of six-month recurrence rate: six-month recurrence rate = number of recurrent AR patients in six months/total number of patients × 100%The RCAT has sufficient reliability, validity, and responsiveness and is a simple patient self-assessment scale [29]. RCAT can be used to assess a patient's rhinitis control status in clinical practice [30]. During the treatment stage, we will collect the RCAT scale online once a week, and during the follow-up stage, we will collect the RCAT scale online every two weeks.

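### Carrying the last RCAT forward counts a controlled patient lost in follow-up as recurrence-free, which biases the primary six-month recurrence rate downward in each arm

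*Protocol article*

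**What the plan says.** The point rests on four statements in the protocol article.

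- **Entry to follow-up** (Abstract, Methods): once the RCAT "score is >21 for two weeks, they will stop taking the medication and enter the follow-up".
- **Event** (section 2.10.2): relapse is an RCAT of 21 or less during follow-up, and "Once a relapse occurs, the patient's recurrence time will be recorded, and the follow-up ends". On frequency, "during the follow-up stage, we will collect the RCAT scale online every two weeks".
- **Estimator** (section 2.10.2): "six-month recurrence rate = number of recurrent AR patients in six months/total number of patients × 100". Section 2.10.3 defines the one-month rate in the same way.
- **Missing data** (section 2.12): "All analyses will be based on the intention-to-treat (ITT) principle", and "For data loss caused by subject drop-out, data from the previous measurement will be carried forward".

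Section 2.6 bases the sample size on six-month rates of 50% (MYN) and 75% (mometasone) and then adds: "To allow for a 10% loss to follow-up, we will recruit 190 subjects in total". Section 2.12 lists Kaplan-Meier and Cox models for time-to-event outcomes, but the primary outcome is defined as a proportion. The carry-forward rule has no exception for the recurrence outcomes.

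**The concern.** Carry-forward can only return a value that the patient has already shown. Here the event itself closes follow-up, so a patient who is still in follow-up and entered it controlled has, by definition, no score of 21 or less since entry. Whatever the time of loss, the carried value is a non-relapse. A patient lost at week 2 counts as six months free of recurrence, although the design expects half to three quarters of patients to relapse.

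This affects the primary endpoint. If loss is equal in the two arms, a true difference shrinks and power falls. If loss is unequal, the arm that loses more patients looks better. Unequal loss is possible here: patients and researchers are unblinded (section 2.8), the RCAT is self-rated, and section 2.15 says "If a patient is uncooperative, the investigators can also end" that patient's participation.

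**Working it through.** **Inputs.** From section 2.6: rates 50% and 75%, superiority margin 5 points, one-sided alpha 2.5%, beta 20%, 86 per arm, 10% loss, 190 in total. From section 2.2: 1:1 allocation, hence 95 per arm. From section 2.12: chi-square test, two-sided 5%. Assumed, because the article does not give them: when losses occur, how they split between arms, and that loss is unrelated to relapse.

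**1. The plan's own figure.** Unpooled formula with margin: (0.75×0.25 + 0.50×0.50) × (1.960 + 0.842)² / (0.25 − 0.05)² = 85.85, so 86 per arm. This reproduces the plan. 86 × 1.1 = 94.6, so 95 per arm and 190 in total.

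**2. What carry-forward does to a rate.** Let p be the true six-month rate and L the proportion lost.

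- *Early loss* (all before any relapse): observed rate = p × (1 − L).
- *Spread loss* (constant hazards over six months): with λ = −ln(1 − p) and loss hazard μ, observed rate = λ/(λ+μ) × (1 − e^−(λ+μ)). Here μ is set so that the proportion actually lost, μ/(λ+μ) × (1 − e^−(λ+μ)), equals L.

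**3. Equal loss of 10%, true rates as planned.**

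- Early: 0.75 × 0.9 = 67.5% and 0.50 × 0.9 = 45.0%; difference 22.5 points instead of 25.
- Spread: 69.5% and 46.9%; difference 22.6 points.

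Power by exact enumeration of two binomials, 95 per arm:

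| Test | No loss | Early loss | Spread loss |
|---|---|---|---|
| 5-point margin, one-sided 2.5% | 83.5% | 71.5% | 72.7% |
| Chi-square, no margin | 95.1% | 88.2% | 88.9% |

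**4. No true effect (75% in both arms).** Probability of a significant result in favour of MYN, 95 per arm:

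| Loss, MYN vs control | Timing | Observed rates, MYN vs control | Chi-square | Margin test |
|---|---|---|---|---|
| None | – | 75% vs 75% | 2.5% | 0.3% |
| 15% vs 5% | early | 63.75% vs 71.25% | 19.9% | 5.8% |
| 15% vs 5% | spread | 66.7% vs 72.3% | 13.1% | 3.2% |
| 20% vs 5% | early | 60.0% vs 71.25% | 37.8% | 15.1% |
| 20% vs 5% | spread | 63.8% vs 72.3% | 24.3% | 7.6% |

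With equal loss and no true effect, the chi-square error stays at about 2.5%.

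**5. Other treatments of the lost patients.** If they are censored and loss is independent of relapse, Kaplan-Meier recovers 75% and 50%. If they are counted as recurrent, with 10% early loss per arm, the rates are 67.5 + 10 = 77.5% and 45 + 10 = 55.0%, a difference of 22.5 points.

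**The case against.** The other side has several good points.

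- **The size depends on assumptions.** The article gives only 10% overall loss and no split by arm. A 20% versus 5% split averages 12.5%, more than the plan expects. Early loss is the extreme case. If the stated percentages are read as the loss that would occur without relapse, fewer patients are actually lost: margin-test power with 10% in both arms is then about 80%, and chi-square false superiority is about 7% (15% versus 5%) and 10% (20% versus 5%). This stands, and it is why ranges are given.
- **The test matters.** Section 2.6 uses a margin and section 2.12 names a chi-square test. Power suffers more under the first, false superiority under the second. Setting the 38% beside the fall in margin-test power would mix the two, so both tests are shown throughout.
- **Loss is mitigated.** The RCAT is collected online, section 2.13 describes retention measures, and section 2.15 asks investigators to contact withdrawn patients and complete what assessments they can. This may reduce loss but does not change how the remaining losses are scored.
- **Kaplan-Meier is already listed.** It is not assigned to the primary outcome, which is a crude proportion.
- **An analysis plan not shown may add detail.** It may, but the published rule is explicit and covers all analyses.

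A reader might also infer two things that the article does not support. The first is that every lost patient is scored recurrence-free. A patient still uncontrolled at the three-month treatment limit and lost before the first follow-up RCAT could carry forward a score of 21 or less, and losses during treatment are a separate case. The second is that carry-forward contradicts the 10% allowance in section 2.6. Inflating recruitment for loss is routine and does not say how lost patients are analysed.

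**Conclusion.** The point holds for patients who enter follow-up controlled and are then lost: the stated rules count them as recurrence-free at six months, however early the loss. Both recurrence rates are biased downward.

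At the plan's own 10% loss, equal in both arms, the cost is about 2.5 points of the difference and 11–12 points of margin-test power, which takes it below the planned 80%; chi-square power stays at 88–89%. The false-positive risk arises only if MYN loses more patients than control. It is 13–20% (chi-square) or 3–6% (margin test) at 15% versus 5%, and 24–38% or 8–15% at 20% versus 5%. Loss in the other direction hides a real benefit.

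These figures assume 95 per arm, loss unrelated to relapse, and the stated percentages actually lost. The direction of the bias in each arm's rate follows from the text alone. It would go too far to infer that the type I error is inflated whatever the loss pattern: equal loss with no true effect leaves it at about 2.5%.

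**What to change.** 1. In section 2.12, exempt the recurrence outcomes from carry-forward.
2. In sections 2.10.2 and 2.10.3, replace the crude ratios with 1 minus the Kaplan-Meier estimate at six months and one month, censoring lost patients at their last RCAT. Removing carry-forward alone is not enough, because observed relapses divided by all patients gives the same bias.
3. Compare the arms by the six-month difference with its 95% confidence interval.
4. Add one sensitivity analysis that counts lost patients as recurrent.

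The cost is a change of wording and a few tables; the method is already named in section 2.12. Kaplan-Meier assumes that loss is non-informative, which the sensitivity analysis probes, and the interval is slightly wider. Because the estimate starts at drug withdrawal, it does not settle how patients lost during treatment or never controlled are counted; the revised definition should say so explicitly.

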#### 2.10.3. Secondary Outcomes

The secondary outcomes are the one-month recurrence rate of AR, the RCAT score, the duration of follow-up (days), the duration of medication (days), the nasal endoscopic results, the visual analog scale (VAS), the total nasal symptom score (TNSS), the rhinoconjunctivitis quality of life questionnaire (RQLQ), the total ocular symptom score (TOSS), the TCM syndrome score of spleen Qi deficiency and lung Qi deficiency, and the classification and determination scale of constitution of TCM.(1)$$\begin{array}{c} \text{Definition of one}-\text{month recurrence rate}=\frac{\text{Number of recurrent AR patients in one month}}{\text{Total number of patients}}\times 100\%. \end{array}$$

All of these will be recorded before/after the intervention and when relapse occurs on the paper version of the CRF.

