#### 2.10.4. Mechanism Outcomes

Serum: endogenous carbon monoxide in serum will be measured by colorimetry. PAF will be measured by quantitative real-time PCR (qRT-PCR). The expression levels of TLR4, CD80, CD86, CCR6, and CCR7 on the surface of DCS will be detected by flow cytometry (FCM).Cells: epithelial nasal mucosa cells will be extracted with a nasal brush. The mRNA and protein expression levels of TLR4, MyD88, and TRIF in the nasal mucosa will be measured by qRT-PCR and Western blotting, respectively. The protein expression levels of HO-1 and TLR2 will be measured by Western blot.Nasal lavage fluid: the nasal lavage fluid concentrations of IL4, IFN*γ*, TNF-*α*, NF-*κ*Β, IL-6, and IL-12 will be measured by ELISA.Not all subjects need to participate in the collection of mechanism samples. A subgroup of 18 subjects will be asked to participate in an optional study, in which the epithelial cells of the nasal mucosa will be extracted with a nasal brush, and the serum and nasal lavage fluid will be collected to measure the mechanism indicators. These samples will be collected at baseline and after drug withdrawal. Regardless of treatment allocation, subjects can voluntarily participate in this part of the trial through instructions provided on the informed consent form. To ensure a consistent baseline, we will use a random number table to randomly select nine willing subjects from each of the experimental and control groups.

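### Continuous scores and markers measured at baseline are compared without baseline adjustment: a valid choice, but less precise than ANCOVA on data already collected

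*Protocol article*

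**What the plan says.** All references are to the protocol article.

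- **Test.** Section 2.12: "Intergroup comparisons of continuous variables will be performed using the" t-test or the Mann-Whitney U test. No covariate, ANCOVA or mixed model is named; the only regression model is Cox, for time-to-event outcomes. The section does not say whether post-treatment values or changes from baseline are compared. Two-tailed p "< 0.05 will be considered statistically significant for all analyses".
- **Baseline data, secondary outcomes.** Section 2.10.3 lists RCAT, VAS, TNSS, RQLQ, TOSS and TCM scores among others, and adds: "All of these will be recorded before/after the intervention and when relapse occurs on the paper version of the CRF". The list also holds two durations, of follow-up and of medication, which can have no baseline value.
- **Baseline data, mechanism outcomes.** Section 2.10.4: "These samples will be collected at baseline and after drug withdrawal". The subset has 18 subjects, and the plan will "randomly select nine willing subjects from each of the experimental and control groups", with comparability of baselines given as the reason for the random draw.
- **Randomisation.** Section 2.8 stratifies by centre only, so baseline scores are not balanced by design.

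**The concern.** A baseline score usually predicts the later score. A two-sample test on post-treatment values ignores that information. A test on changes uses it, but with a fixed weight of one, which is too much whenever the correlation is below 1 (equal SDs). In both cases the estimate has a wider interval than necessary, and a chance difference at baseline stays partly in the result.

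The scores support the efficacy claim beyond recurrence, and the markers support the mechanism claim. The mechanism subset is the most exposed: random selection of nine per arm balances baselines only in expectation, not in the sample obtained.

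**Working it through.** **The plan's own figure.** The article gives no calculation for continuous outcomes. Its only sample size is for the binary primary outcome, where "the six-month recurrence rates of AR treated with MYN and mometasone furoate aqueous nasal spray were approximately 50% and 75"%, with a 5% margin and "an acceptable alpha of 2.5% (one-tailed), and an acceptable beta of 20%, 86 participants were required in each group". It reproduces: (0.75×0.25 + 0.50×0.50) × (1.960 + 0.842)² / (0.25 − 0.05)² = 85.85, rounded up to 86; 86 × 1.1 gives 95 per arm, 190 in total. Nothing below changes it.

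**Inputs.** n = 95 per arm (half of 190); n = 9 per arm in the mechanism subset; two-sided alpha 0.05. The baseline-outcome correlation r is not in the article and is an assumption. The SD is taken as equal at both visits, and results are in SD units.

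**Formulas (large sample), SE of the difference between arms**
- t-test on post values: √(2/n)
- t-test on changes: √(4(1 − r)/n)
- ANCOVA: √(2(1 − r²)/n)

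The variance ratios are therefore 1 − r² (ANCOVA to post values) and (1 − r²)/(2(1 − r)) = (1 + r)/2 (ANCOVA to changes).

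**Full sample, 95 per arm**

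| r | SE post | SE change | SE ANCOVA | Ratio to post | Ratio to change | Power if post-value test has 80% |
|---|---|---|---|---|---|---|
| 0.3 | 0.145 | 0.172 | 0.138 | 0.91 | 0.65 | 83.6% |
| 0.5 | 0.145 | 0.145 | 0.126 | 0.75 | 0.75 | 89.9% |
| 0.7 | 0.145 | 0.112 | 0.104 | 0.51 | 0.85 | 97.5% |

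At r = 0.5 the gain equals 1/0.75 = 1.33, or 33% more patients. The ratios are for the t-test. The Mann-Whitney test on the same values omits the covariate in the same way, but no ratio was computed for it.

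**Chance baseline difference.** Its 95% limits are ±1.96√(2/n): ±0.28 SD at 95 per arm and ±0.92 SD at 9 per arm. Given a baseline gap D, the expected error is rD in a post-value comparison and rD − D = −(1 − r)D in a change comparison. At r = 0.5 that is up to 0.14 SD (n = 95) or 0.46 SD (n = 9), in opposite directions for the two methods. ANCOVA removes this linear part.

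**Mechanism subset, 9 per arm.** The unadjusted t-test has 80% power only for a standardised difference of 1.41. The large-sample ratios do not carry over directly:
- Adjusting for baseline alone multiplies the variance by about 1 + 1/14. The SE goes from 0.471 to 0.465 SD at r = 0.3 and 0.423 at r = 0.5, but rises to 0.488 if r = 0.
- Adding three centres makes five parameters on 18 subjects, leaving 13 residual degrees of freedom.

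Simulated mean width of the 95% interval, in SD units, with centre unrelated to outcome:

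| Model | r = 0.3 | r = 0.5 |
|---|---|---|
| Unadjusted | 1.96 | 1.95 |
| Arm + baseline | 1.95 | 1.76 |
| Arm + baseline + centre | 2.12 | 1.93 |

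The model with centre is wider than the t-test until r reaches about 0.45.

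**The case against.** The strongest reply is that nothing here is an error. A reader might infer that the stated tests are biased or inflate the type I error. They do neither: under randomisation they are valid and unbiased on average, and the loss is of precision and of protection against the imbalance that happens to occur. This part of the reply stands, and it keeps the point modest.

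A reader might also infer that the plan throws the baseline away. The article does not support that either, since Section 2.12 leaves open whether values or changes are tested, and a test on changes uses the baseline. A condensed article may well leave that detail to the analysis plan. The point survives because ANCOVA has the smaller large-sample variance on both readings, and because the article does name the test.

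Three further limits stand:
- The size of the gain depends on an r that the article does not give. At r = 0.3 the SE falls by only 4.6% against post values. For RCAT at withdrawal r may be low, because treatment stops early only once RCAT exceeds 21, which narrows the range.
- Scores taken at relapse exist only for those who relapse, a group formed after randomisation. Baseline adjustment does not make that comparison a randomised one.
- One might expect adjustment to tighten every interval. At nine per arm it does not once centre terms are included.

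**Conclusion.** The point holds as a matter of efficiency. For end-of-treatment scores with a baseline value, the stated tests are valid but less precise than ANCOVA, whether applied to post values (variance ratio 1 − r²) or to changes ((1 + r)/2). Over assumed r of 0.3 to 0.7, ANCOVA cuts the variance by 9% to 49% against post values and by 35% to 15% against changes. These figures assume equal SDs, a linear relation and large samples.

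In the mechanism subset, adjustment for the baseline marker alone is about neutral at r = 0.3, helps above that, and loses a little if r is near zero. Random selection of nine per arm cannot ensure comparable baselines there. The primary outcome, the sample size and the two duration outcomes are outside the point. It is a worthwhile improvement, not a correction of an invalid analysis.

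**What to change.** 1. **End-of-treatment scores, full randomised sample** (VAS, TNSS, TOSS, RQLQ, RCAT, TCM scores): replace the t-test or Mann-Whitney test by ANCOVA with arm, baseline score and centre (the randomisation stratum). Report the adjusted mean difference with its 95% CI, and use a rank-based or log-scale version if the data are skewed.
2. **Exclude** duration of follow-up, duration of medication and scores taken at relapse from this model.
3. **Mechanism subset:** fit arm and baseline marker only, without centre terms, and accept a small loss of precision if r is near zero. Drop the reliance on random selection as a guarantee of comparable baselines.
4. **Timing:** fix this before outcome data are seen, so that the choice to adjust cannot look selective.

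The cost is a change of wording in Sections 2.10.4 and 2.12 or in the analysis plan. The stated software, SPSS 25, fits ANCOVA, and no new data, visits or patients are needed.
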